## Abstract

**Background:**

This paper describes the design and methods of a multi-phase study to reduce early childhood caries and obesity in vulnerable South Asian (SA) immigrants in the United States. Early childhood caries and obesity are the most common diseases of early childhood. Risk factors for both diseases are rooted in early childhood feeding practices such as bottle feeding and intake of sweets and sweetened beverages. The Common Health/Risk Factor Approach to addressing oral health is widely promoted by the WHO and other policy makers. This approach recognizes links between oral health and other diseases of modernity. Our CHALO! (“Child Health Action to Lower Obesity and Oral health risk”--from a Hindi word meaning "Let's go!") study targets SA families at high risk for early childhood caries and obesity. CHALO! addresses common risk factors associated with these two common diseases of childhood.

**Methods:**

This two part project includes a randomized controlled trial, and a Knowledge Translation campaign. A randomized controlled trial will enroll *n* =  360 families from pediatric practices serving South Asians in the New York metro area. The intervention group will receive home visits by SA community health workers at 6, 8, 10, 12, 14, and 16 months of age. Controls will receive culturally tailored educational material. Primary outcomes-- cariogenic and obesogenic feeding practices at 6, 12, and 18 months-- will be assessed with the MySmileBuddy iPad based tool. Secondary outcomes include: oral hygiene practices, anthropometrics, and caries incidence at 18 months. A public education campaign will focus on both families and health care providers.

**Discussion:**

There are few Common Health/Risk Factor Approach published studies on obesity and oral health risk in children, despite health morbidity and costs associated with both conditions. CHALO! comprises a multi-level interventions designed to promote culturally competent, sustainable change.

**Trial registration:**

ClinicalTrials.gov
NCT03077425.

**Electronic supplementary material:**

The online version of this article (10.1186/s12889-018-5317-9) contains supplementary material, which is available to authorized users.

## Background

Immigrants from the developing world are impacted by the global *nutrition transition,* from low calorie, highly nutritious foods in resource-poor environments, to the high calorie, low nutrition diets of the west [1]. Nutrition-related diseases occur with the adoption of western diets. Obesity and oral caries, the most common diseases of early childhood in western societies, are prevalent in low income immigrant communities [2–4]. The Child Health Action to Lower risk of Obesity and Oral caries--**CHALO!** (“let’s go!” in Hindi)-- is a multi-level intervention culturally tailored for at-risk immigrant South Asians (SAs) from India, Pakistan, and Bangladesh. These SAs are among the fastest growing immigrant groups in the US [5, 6].

SAs are particularly vulnerable to nutrition-related disease. A modernizing diet in urban South Asian has created a public health ‘tsunami’ of obesity and metabolic disorders in that region [7–9]. SA immigrants in the UK and Canada bear a high burden of obesity-related health disparities [10–12]. SA immigrant children demonstrate growth patterns associated with metabolic risk: low birthweight followed by steep weight gain in infancy and childhood [13]. A tendency towards central adiposity places adults and children at high risk for metabolic syndrome even controlling for body mass index (BMI) [9, 14]. Children are also at high risk for early childhood caries (ECC) [15–17], even adjusting for socio-economic status s [18].

### The common risk factor approach

The Common Risk/Health Factor Approach (CR/HFA) to oral health disparities focuses on risk factors and underlying social determinants shared with other diseases of modernity [19]. Based on the CR/HFA, CHALO! employs a multi-level social-ecological framework for conceptualizing and addressing oral health and obesity risk (See Table 1):

**Table 1 Tab1:** Outline CHALO Multi Level Intervention

Activity	Target	Level
Home Visit with Mothers	Knowledge, support, wellbeing, confidence, skills, feeding behaviors	Individual
Home Visits with Families	Family/household support for Mothers’ Goals	Interpersonal
Dental Referral & Navigation	Link families to providers; facilitate appointments	Organizational
Knowledge Translation --Community	Raise awareness & educate via: 1-to-1 outreach, local meetings, video/drama	Community
Professional Dissemination	Educate local providers on AAP & AAPD policy; raise cultural awareness; promote professionals-researcher-policymaker dialogue	Community & Policy

#### Individual level influences

Maternal feeding practices in early life increase the risk of caries (i.e., cariogenic) and obesity (i.e., obesogenic). They include: prolonged use of bottles (and ‘sippy cups’); adding solids and sweets to bottles; nighttime feeding; salty and starchy snacks; sweets, and sweetened beverages. Bottle use beyond 12–15 months increases risk for both conditions [20–26], as do bottles at night or naptime [22] or bottles that contain solids [27] and sweeteners [28]. Bottle feeding *facilitates overriding of a child’s internal satiety cues,* [29] thereby reducing ability to self-regulate intake [30]. This may further promote both weight gain [31, 32] and early childhood caries (ECC) [24].

Such feeding practices are common in SA communities [33, 34]. Up to 75% of low-income SA 15-month olds still use a bottle, and 30% regularly drink sweetened milk [35–37]. *Non-responsive feeding* is also common in SA families. Non-responsive feeding’s defining feature is caregiver lack of responsiveness to a child’s feeding cues. It includes both adult controlling (forcing or restricting) and child controlling (indulgent) feeding [38]. Forcing/controlling feeding leads to rapid weight gain in the first year of life, which predispose to overweight in later years [39, 40]. Indulgent styles are associated with obesity in toddlers and older children [41]. Among SAs in the New York area, ‘force feeding’ is routine. Once children are old enough to ask for food, force-feeding yields to indulgent feeding. SA mothers fear distressing their children by refusing food [42].

In addition to common risk behaviors, there are unique risk behaviors associated with obesity and caries that are common among SA immigrants. SA children are more sedentary than their white counterparts, raising their risk of obesity [43–46]. Oral health prevention—e.g., brushing, oral hygiene, and preventive dental care—are undervalued in SA communities. Many families seek dental care only when there is pain or visible decay; baby teeth may be viewed as dispensable [42, 47, 48].

#### Interpersonal level influences

SA married women’s low status and limited access to family decision-making may impede adherence to medical advice [42]. Senior family members may insist traditional feeding patterns including frequent sweets and delayed weaning [37, 42]. Maternal depression—due to factors such as poverty, isolation, and marital abuse—is common in SA families [49–51]. Maternal depression is associated with non-responsive feeding [52, 53] and child obesity [41]. Poverty and its sequelae, including substandard housing, further limit mothers’ ability to change feeding patterns. Such may cause disruption and crying, which may be difficult to tolerate in crowded living quarters [42].

#### Institutional/organizational level influences

Like other low-income immigrants, SA children lack access to dental care [4, 54, 55]. Pediatricians rarely refer to dentists [4, 54–57]. Guidelines recommend a first dental visit by 12 months of age and two visits per year for low-income and immigrant children [58, 59]. Yet only 1.5% of one-year olds visit a dentist each year [60] and rates are lowest in poor families who could most benefit [61]. Another barrier to care for low income children is the fact that many dentists on the US don’t accept Medicaid or Children’s Health Insurance Program coverage [62].

#### Community level influences

These include cultural beliefs and practices, along with low awareness of risk factors. Though concerns over child feeding are widely shared among SA mothers, there is relatively little understanding of how non-responsive feeding leads to child food refusal, creating a vicious cycle of increased maternal anxiety and force feeding. One SA mother on www.indusladies.com, a website for South Asian moms, asks: "Why do American kids happily feed themselves from the age of one year old and are constantly asking for food? Why do Indian kids hate food and need to be FORCE FED until the age of 4,5,6, or even 7?" Pediatricians in the SA community often report frustration. “*Feeding problems take up 75% of my time*.” ([name], SAPPHIRE network pediatrician. In.; 2015, personal communication). Physicians lack tools and support needed to address this problem. *“The most commonly prescribed medication in my practice is an appetite stimulant. Even though the child doesn’t need it, I have to prescribe to get peace in the family.”* ([name]. In.; 2015, personal communication).

#### Policy level influences

The Knowledge Translation campaign will work with private practitioners, residents, and teaching faculty in dental and pediatric departments. Through dialogue and presentations in clinical and educational settings, the goal is to develop new best practices and guidelines regarding the improved care of South Asian immigrant children.

The randomized controlled trial (RCT), CHALO! will answer the following research questions: a) Does a culturally-tailored CR/HFA home-visiting intervention, from child age 6 through 16 months, reduce cariogenic and obesogenic behaviors in SA immigrant families (primary hypothesis)? b) Is this CR/HFA intervention associated with reduced incidence of oral caries and obesity at 18 months of age (secondary hypothesis)?

## The CHALO project RCT

### Methods

To address individual and interpersonal (i.e., household) risk factors, SA community health workers (CHWs) will conduct a home-visiting intervention. Home Visiting is a decades-old strategy to improve maternal-child health outcomes [63–65] by empowering families. We will recruit low-income SA mother-child dyads from pediatric practices in New York City and New Jersey (U.S.). Inclusion criteria include: a) *Age*: Child is < 6 months old at time of recruitment; b) *Insurance*: Child is enrolled in either Medicaid or the Children’s Health Insurance Program; c) *Nativity*: Mother was born in India, Pakistan, or Bangladesh); d) *Language*: Mother speaks standard Bengali, English or Hindi/Urdu; e) *Agency*: Mother is index child’s primary caretaker. Exclusion criteria include: a) Inability to provide informed consent; b) Plans to travel for > 1 month during follow-up, and; c) child health condition barring participation (per pediatrician review).

#### Enhanced usual care (control)

An EUC counseling intervention will be delivered immediately following the T0 Baseline Interview, just prior to randomization. EUC Components include: 1) a pamphlet- containing basic ECC and Obesity prevention messages, and 2) Dental Referrals. We developed a Screened Dental Provider list of dentists who: a) are willing to see 12 month old children; and b) accept most insurance plans in the study practices.

#### Intervention

CHWs will conduct *n* = 6 home visits when the child is 6, 8, 10, 12, 14, and 16 months old. Of these, 4 visits include only the mother-child dyad. Visits at 8 and 14 months will include a senior family decision maker (e.g., husband or mother-in-law). CHWs will conduct 6 follow up telephone calls in alternate months. Calls will be used to ask about the family’s goals for change, gauge progress, and assist with trouble shooting.

*Mother-only visits* will focus on building rapport and intimacy, identifying family/household concerns, reviewing risk/health behaviors, reviewing, setting, and troubleshooting goals, building skills through active interaction with the child, and providing education. Messages will be provided orally and via culturally tailored, attractive educational materials. To bolster mothers’ skills, CHW-guided interactions with the dyads will include: recognizing infant satiety and hunger cues via responsive bottle feeding, preparing age-appropriate self-feeding foods, encouraging tummy time and active play, transitioning from naptime milk to water bottles, and oral hygiene practices such as tooth brushing. At each visit, the CHW encourages the mother to set a concrete, manageable behavior change goal. Patient navigation, as needed, will encourage mothers to make and keep two dental visits for their child, over the 12 month follow-up. *Family visits* will, similarly, assess family views on barriers to change, and enlist support for mothers’ child feeding goals (Fig. 1).

**Fig. 1 Fig1:**
[figure not shown]
Study flow

### Outcomes measurement:

The RCT’s **primary aim** is to reduce risk behaviors for caries and obesity. We hypothesize that relative to Controls, the Intervention group will report: less bottle use (any, with added sweeteners/solids, at nap and bedtimes), improved food choices (*more* fruits and vegetables, *less* juice and sweetened beverages, *fewer* sweet and salty snacks); *more* physical activity and *less* screen time; and *more* tooth brushing and dental visits. See Table 2 for Schedule of Research Assessments.

**Table 2 Tab2:** Schedule of Research Assessments: 6, 12, and 18 Months

Interview	Data Obtained	Setting
Baseline @ 6 mos. (T0)	Questionnaires	Home
	MySmileBuddy (MSB)	
	Weight/length	
12 mo. Interview (T1)	Questionnaires	Home
	MySmileBuddy (MSB)	
	Weight/length	
18 mo. Interview (T2)	Questionnaires	Home
	MySmileBuddy (MSB)	
	Caries Exam	
	Weight/length	

#### Common risk factor feeding behaviors

We will use MySmileBuddy (MSB), an iPad based ECC risk assessment and educational tool [66]. MSB was validated in previous research [67]. The MSB guides parents through a modified 24-h dietary recall for their child. We have adapted the MSB to reflect culturally appropriate SA foods and beverages, as well as the types of bottles and cups used for beverages. Participants are cued by queries (e.g., first thing to eat or drink upon waking) and attractive color photographs of food and beverage groupings. Prior to administration, the research assistant will ask whether the prior 24 h represented a ‘usual day.’ If not, participants will conduct a recall for one day earlier. We will conduct a second 24-h recall for a subset of participants.

*Unique risk factors for obesity* (sedentary behavior/screen time) will be assessed through previously validated questionnaire items used in other large studies. *Unique ECC-risk factors* include dental visits and oral hygiene practices. We will assess frequency of tooth brushing, use of toothpaste, and use of tap water using items from a measure developed by the CDC. Dental health utilization will be assessed through questions at T1 and T2.

The RCT’s **secondary aim** is to reduce the velocity of weight gain in months 12–18, and the incidence of oral caries at 18 months. Weight and length data will be collected by research assistants at the T0, T1, and T2 outcomes assessments. Study pediatricians will train research staff in anthropometrics protocol. For length, two supine measures will be taken using infantometers (Seca 417, Brooklyn NY), to the nearest 0.1 cm. For weight, children will be measured with diaper and light clothing. ECC will be assessed by study staff using Intraoral cameras at the 18 month follow-up. Intraoral cameras are valid [68–72] and acceptable [73] in young children. Images will be transmitted to pediatric dentists at the Kodiak who will determine the presence of visible dental caries and (if any) their severity (Table 3).

**Table 3 Tab3:** Common Risk/Health Factor Measures

Construct	Variable Measure	Source
Bottle/Sippy:	Any (Y/N)	24 h recall (MSB)
	Frequency (#/day)	24 h recall (MSB)
	Added sweet/solid (Y/N)	24 h recall (MSB)
	@ Bed or Nap (Y/N)	24 h recall (MSB)
Dietary Pattern	F & V servings (#/day)	24 h recall (MSB)
	Juice & sweet drinks (#/day)	24 h recall (MSB)
	Sweet & salty snack (#/day)	24 h recall (MSB)
Unique Obesity	Physical activity	Questionnaire
	Screen time	Questionnaire
	BMI-for-Age Z score	Pediatrics visit
	Weight Velocity Z score	Pediatrics visit
Unique Oral Health	Oral hygiene (#/day or wk)	Questionnaire
	Dental visit (Y/N)	Questionnaire
	Visible caries (Y/N)	Intra-oral camera
	Caries Severity (dfs index)	I.O. camera

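### The 18-month caries outcome is worded so that a restored lesion can be scored as no caries, and any such error would tend to favour the intervention arm

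*Protocol article*

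**What the plan says.** The second research question, at the end of the section on policy level influences, asks whether the intervention is "associated with reduced incidence of oral caries and obesity at 18 months of age". The secondary aim repeats the caries part: "and the incidence of oral caries at 18 months".

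Measurement is described under the common risk factor feeding behaviors heading: "ECC will be assessed by study staff using Intraoral cameras at the 18 month follow-up". Table 2 lists a caries exam at T2 only. The images go to pediatric dentists, "who will determine the presence of visible dental caries and (if any) their severity". Table 3 lists two variables from the camera: "Visible caries (Y/N") and "Caries Severity (dfs index"). The article does not expand dfs; its conventional meaning is decayed and filled surfaces.

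On dental care, the Intervention section states: "Patient navigation, as needed, will encourage mothers to make and keep two dental visits for their child, over the 12 month follow-up". The enhanced usual care section gives a pamphlet, dental referrals and a screened dentist list before randomization, so both arms have them. The Outcomes measurement section hypothesises more dental visits in the intervention group. Dental use is asked about at T1 and T2.

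**The concern.** Incidence by 18 months means that a child has developed caries at some time up to that age. A single reading of visible caries measures the disease still on view at that age. The two differ for a child whose lesion arose and was restored before the exam.

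The text makes severity conditional on visible caries being found. Read plainly, a child with only restored teeth has no visible caries and therefore no dfs score, even though the f in dfs exists to count such surfaces. The sentence and the chosen index pull in different directions.

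This would matter little if treatment before T2 were equally likely in both arms. But navigation to dental visits is part of the intervention as described, and more visits are one of its intended effects. Better access to treatment could then be reported partly as fewer children with caries, on the trial's only oral-disease outcome. Readers who do not know the arm would not correct this, because it comes from what the images show and how a filled surface is classed.

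**Working it through.** **The plan's own figures.** The article gives no calculation for caries. Its one design calculation, for daily bottle and sippy cup use, reproduces: with 150 per arm and d = 0.7/2 = 0.35, 0.35 × √(150/2) = 3.031; 3.031 − 1.960 = 1.071; Φ(1.071) = 85.8%, against the stated figure of more than 85%. It does not bear on this point beyond supplying the 150 per arm used below.

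**The scoring rule, applied to three kinds of child at T2**

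| State at T2 | Visible caries, plain reading | dfs, if scored only when caries is visible | dfs, if scored in every child |
|---|---|---|---|
| Never had caries | No | not scored | 0 |
| Untreated lesion | Yes | > 0 | > 0 |
| All lesions restored | No (not stated) | not scored | > 0 |

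Only the third row changes with the rule. The article does not say how that child is classed.

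**Possible size (all rates assumed).** Let the true risk of ever having caries be p in both arms. Let f_C and f_I be the shares of affected control and intervention children whose lesions are all restored before T2 and then scored as no visible caries. The observed risks are p(1 − f_C) and p(1 − f_I), so the apparent risk ratio is (1 − f_I)/(1 − f_C), whatever p is.

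The last column is the chance of a result significant at two-sided 0.05 in the intervention's favour with 150 per arm: Φ[(difference − 1.96 × SE₀)/SE₁], with SE₀ pooled and SE₁ unpooled. With no true effect and no misclassification it would be 2.5%.

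| p | f_C | f_I | Observed control | Observed intervention | Risk ratio | Chance |
|---|---|---|---|---|---|---|
| 5% | 0 | 5% | 5.0% | 4.75% | 0.95 | 3.1% |
| 10% | 0 | 10% | 10.0% | 9.0% | 0.90 | 4.8% |
| 10% | 5% | 20% | 9.5% | 8.0% | 0.84 | 6.7% |
| 10% | 5% | 30% | 9.5% | 7.0% | 0.74 | 12.0% |
| 20% | 5% | 30% | 19.0% | 14.0% | 0.74 | 21.3% |

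On the odds ratio scale, which fits the planned logistic regression, two further cases with p = 10%:
- 10% against 30% treated: 9% against 7%, odds ratio (0.07/0.93)/(0.09/0.91) = 0.76.
- 5% against 15% treated: 9.5% against 8.5%, odds ratio (0.085/0.915)/(0.095/0.905) = 0.88.

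If every examined child is scored and dfs > 0 defines a case, restored children stay cases and the risk ratio in all these scenarios is 1.0.

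**The case against.** The strongest reply is that Table 3 lists the dfs index. Choosing an index with a filled component suggests that restored surfaces were meant to count, and the parenthesis in the text may be only a loose summary of the readers' task. This stands to the extent that one cannot say filled surfaces are never scored; a reader might infer that, but the article does not state it. It does not remove the point, because the sentence that describes the scoring makes severity conditional, and the yes/no variable is left open for filled teeth.

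Second, coding of restored teeth could be called detail for an examiner manual or the full protocol. That would be fair if the article were silent. It states a rule, and that rule fits poorly with both the index and the word incidence.

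Third, the mechanism is not documented. No restoration rate is given. The hypothesis is more visits, not more restorations. Both arms receive referrals and the dentist list, so the arms differ in as-needed navigation rather than in having a route to care. The background also says many families seek care for pain or visible decay, which can happen in either arm. All of this stands and limits the size.

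Fourth, the illustration assumes that all lesions in a treated child are cleared and that readers ignore every filling. Even then, 9% against 7% of 150 is 13.5 against 10.5 children, an odds ratio of 0.76 with a 95% interval of roughly 0.33 to 1.8. This also stands.

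**Conclusion.** The point holds as a weakness in the definition of a secondary outcome. As worded, a child with only restored lesions can be scored caries-free, and the conditional severity score does not sit well with the index chosen. Because navigation is described for one arm only and more visits are expected there, misclassification would tend to favour the intervention.

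The size is unknown. The risk ratios of 0.95 to 0.74, and the 3% to 21% chance of a spurious significant result, rest on assumed caries and treatment rates and on the plain reading of the scoring sentence. If few lesions are treated by 18 months, the effect is probably small.

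A reader might go further and conclude that the trial will count treated caries as prevented caries, or that controls have no route to dental care. The article supports neither: it does not say how filled teeth are classed, and enhanced usual care gives both arms referrals and a dentist list. The primary outcome is not affected.

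**What to change.** - Instruct the image readers to score dfs in every examined child, not only where visible decay is found.
- Define the binary caries outcome as caries experience: dfs > 0, meaning any decayed or filled surface on the 18-month images.
- Report untreated visible caries as a separate descriptive outcome.
- If wanted, add one item on fillings or extractions for decay to the dental-use questions at T1 and T2, and use it only in a sensitivity analysis. It could pick up extractions, which dfs does not count, and treatment that leaves no visible restoration. It should not enter the main definition. Parents know their arm, and an arm with more dental visits has more chances for lesions to be found, treated and reported, which could bias the result against the intervention.

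The cost is a change of definition and a scoring instruction, using images already planned, plus at most one questionnaire item. No clinical care changes. What remains is that dfs > 0 still misses extracted teeth and treatment not visible on the images.
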